### Recruitment and data collection

Following their discharge, patients in a romantic relationship who provided institutional consent to be approached for research are directly contacted in-person or by phone by a research coordinator (RC). For those who do not provide such consent, a member of their circle of care initiates contact and obtains permission for the RC to contact the patient to provide information about the study. Recruitment strategies are adopted to achieve adequate participant enrolment, such as approaching patients at scheduled follow-up appointments and emailing additional information to those who indicate initial interest and confirm email consent. If patients express interest in participating following initial contact, the RC then explains the study procedures and obtains informed consent from the patient and partner. Participants are then invited to fill out an online questionnaire package via Research Electronic Data Capture (REDCap), a secure web-based application designed to support data capture for research studies. Those who prefer may complete the questionnaires on paper; these data are entered into REDCap by the RC. If DAS scores are above the established cut off, participation is concluded. Those in the eligible range are invited to complete the full study and scheduled for a baseline appointment at the UOHI.

#### Baseline assessment

Prior to the baseline assessment, participants fast, abstain from exercise for 12 h, and avoid caffeine and non-prescription diuretics for 4 h. At the assessment, they review and sign two copies of the study consent form. After obtaining signed consent, participants provide a blood sample (10 mL) and rinse their mouth in preparation for the saliva samples. Staff then attach pre-gelled electrodes under the participant’s right clavicle and below the left ribcage for HRV recordings. Saliva samples are collected 10 min after arrival. Then, participants complete the spousal disagreement form, followed by a 15-min rest period during which participants sit quietly but avoid sleeping. The conflict resolution task is completed next. Immediately before and after the conflict resolution task, blood pressure (BP) and heart rate readings are recorded, and additional saliva samples are taken. Participants are asked to rest for another 15 min upon completion of the second set of BP readings. Two final saliva samples are collected at 20 and 40 min after the conflict resolution task (Birkett, 2011). Finally, height, weight, waist circumference, and carbon monoxide levels are recorded, and patients are given an accelerometer to wear for a 7-day period. Bloodwork is collected by staff phlebotomist, and assessments are carried out by research staff with backgrounds in nursing, psychology, and health sciences. Study staff are trained on assessment procedures, including the reading of BP results and protocols for abnormal values or adverse events during the appointments. At the end of the baseline assessment, the RC randomizes participants to the HHT or UC and informs them of group assignment. Randomly generated intervention allocations are contained within sealed opaque envelopes. Research staff who assist with assessments are not present during randomization. Couples in the intervention arm receive information about HHT group logistics.

#### Follow-up assessments

The same procedures are conducted at each follow-up assessment (8 weeks and 6 months). A REDCap link is sent to participants via email or, if preferred, printed questionnaires are sent by post to be completed before the assessment. Patients also report if they enrolled in CR and, if so, in which program options they participated (e.g., exercise, nutrition, stress management class). They also indicate if they partook in any individual or couples-based psychological services. Research staff conducting follow up data collection, intervention infidelity checks, and behavioral coding are blind to the randomized condition. To maximize participant retention, assessments are scheduled to coincide with regular follow-up appointments or rehabilitation sessions at the UOHI whenever possible. Appointment reminders and parking passes are provided at each assessment, and gift cards are distributed after their final assessment. Efforts are made to collect primary outcome data despite potential deviation from study protocols. For example, the completion of online questionnaires will still be offered to those who might withdraw from in-person study activities.

#### Data management

Following study assessments, research assistants enter data into SPSS. Other staff members periodically carry out quality checks, and discrepancies are recorded and reported to the staff leading data entry. After assessment completion and data entry, files with participant information are stored in locked cabinets on site. To maintain confidentiality, all data entered is coded with study ID numbers instead of personal identifying information.

### Interventions

#### Healing hearts together intervention

Couples are invited to attend 8 weekly 2-h sessions facilitated by clinical psychologists with EFT training. Before providing the intervention, facilitators review information on CVD and its treatments, theory and practice of group interventions, and familiarize themselves with the HHT facilitator materials. An HHT facilitators manual was developed to standardize intervention delivery (Tulloch et al., 2017). Planned group size is 3–8 couples, with sessions available in the day or evening to accommodate participants’ work schedules. Since the onset of the COVID-19 pandemic (March 2020), however, groups have been conducted online using the secure platform Zoom; only one group was held in-person before the pandemic. During the program, participants are guided through seven conversations in which they learn to identify and improve communication patterns for positive interactions in relationships (Tulloch et al., 2021). EFT interventions allow couples to acknowledge their fears and vulnerabilities and solidify their sense of security and emotional connection by guiding partners to respond to these feelings in comforting ways (Johnson, 2004; Johnson, 2008). The intervention maintains principles from the *Hold Me Tight* program (Johnson, 2010) but, as alluded to above, centres on identifying the impact of CVD on relationship dynamics, including the recognition and processing of worries and emotions following a cardiac diagnosis or event, healing interactions, and discussing sexuality in a health context (Tulloch et al., 2021). Materials, such as in-class and take-home worksheets, didactic presentations, and videos, are incorporated to facilitate these conversations (Johnson, 2010; Tulloch et al., 2021). The session-by-session overview has been previously described (Tulloch et al., 2021). In brief, each session begins with a review of the previous session and its homework, followed by a didactic presentation, a video clip of a couple discussing EFT principles, a private dyadic conversation, a final group discussion, and a homework assignment. In addition, each couple receives a copy of the book, *Hold Me Tight*, in print or audio version (Johnson, 2008) to be read in-between sessions. Attendance is noted at each session. Participants are asked to inform research staff if they must miss a session, and if this is the case, they are sent presentation slides from the respective session for review. Participant feedback surveys are sent via email after each session. All sessions incorporate group discussions and private conversations between patients and partners. Group discussion allows couples to share experiences related to CVD with their partners and peers. Session two allows for participants to discuss their experiences as patients in a patient-only group and as partners of someone with CVD in a partner-only group discussion, both of which are guided by a facilitator. Zoom break-out rooms are used for dyadic-specific exercises; facilitators assist during these discussions. HHT intervention materials may be found here: https://iceeft.com/healing-hearts-together-relationship-education-program/.

#### Usual care

All patients at the study hospital are scheduled for a follow-up visit 4–8 weeks after hospitalization. At this appointment, a physician conducts a clinical assessment and determines appropriate medical management. Patients are automatically referred to the centre’s CR program, which includes exercise training and potential referrals to medical and allied health services, including dietetics, social work, psychology, and vocational rehabilitation; patients may choose whether they wish to receive these services or not. Optional attendance at nursing-led patient/caregiver support groups (e.g., heart failure support) and peer-support groups (e.g., Women at Heart) is also available. While the control group is potentially extensive, it represents evidence-based care for patients with CVD and, as such, preventing participants from enrollment would be unethical.

### Measures

Assessments are conducted at baseline before randomization, and at 8 weeks and 6 months; the timeline for all measures is presented in Table 1. As previous couples-based research often failed to include partners in their measurements, all participants complete measures assessing relationship variables, mental health, general Quality of Life (QoL), and health behaviors; are monitored for HRV, heart rate, and BP; and provide salivary and plasma samples. Disease-specific QoL, medication compliance, and CR adherence (if enrolled) is collected for patients only.

**Table 1 tab1:** Study measures and timeline.

Procedure/measure	Patient				Partner			
	Screen	BL	Week 8	Week 24	Screen	BL	Week 8	Week 24
Eligibility criteria	✓	✓			✓	✓		
Informed consent		✓				✓		
Demographics		✓				✓		
Medical history		✓				✓		
Follow-up medical questionnaire			✓	✓			✓	✓
Dyadic Adjustment Scale (DAS)		✓	✓	✓		✓	✓	✓
Traditional Masculinity-Femininity Scale (TMF)		✓				✓		
Salivary cortisol, HRV, and BP (pre-post a conflict-resolution task)		✓	✓	✓		✓	✓	✓
Brief Romantic Relationship Interaction Coding Scheme (BRRICS)		✓	✓	✓		✓	✓	✓
Experiences in Close Relationships Scale-12 (ECR-12)		✓	✓	✓		✓	✓	✓
Global Measure of Sexual Satisfaction (GMSEX)		✓	✓	✓		✓	✓	✓
Self-Efficacy in Romantic Relationships scale (SERR)		✓	✓	✓		✓	✓	✓
Beck Depression Inventory Second Edition (BDI-II)		✓	✓	✓		✓	✓	✓
Patient Health Questionnaire (PHQ-9)		✓	✓	✓		✓	✓	✓
General Anxiety Disorder 7 item (GAD-7)		✓	✓	✓		✓	✓	✓
Cardiac Anxiety Questionnaire (CAQ)		✓	✓	✓				
PTSD Checklist for DSM-5 (PCL-5)		✓	✓	✓		✓	✓	✓
Zarit Burden Interview (ZBI)						✓	✓	✓
Short Form 36 Health Survey (SF-36)		✓	✓	✓		✓	✓	✓
Heart-related Quality of Life Scale (HeartQoL)		✓	✓	✓				
Quality of Life of Cardiac Partners Questionnaire (QL-SP)						✓	✓	✓
Smoking status		✓	✓	✓		✓	✓	✓
Physical activity (ActiGraph GT3X-BT)		✓	✓	✓		✓	✓	✓
Cardiovascular markers (blood work)		✓	✓	✓		✓	✓	✓
Godin Leisure Time Exercise Questionnaire		✓	✓	✓		✓	✓	✓
Medication adherence		✓	✓	✓				
CR adherence		✓	✓	✓				
HHT end-of intervention measures (8 weeks)	Group Climate Questionnaire (GCQ) HHT Satisfaction Survey HHT intervention fidelity checklist							

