Indirect pathways in which RQ influences heart health involve health behaviors driven by RQ (Azizi et al., 2024; Khaing et al., 2017; Rapelli et al., 2022; Bertoni et al., 2023). Relationship problems can lead to engagement in risky health behaviors such as smoking and alcohol use (Roberson et al., 2018), whereas better marital adjustment and positive dyadic coping is associated with enhanced medication compliance (Rapelli et al., 2022) and cardiac rehabilitation (CR) (Trevino et al., 1990). Spouses can exert social influence over health behaviors, such as preparing low-sodium meals, modeling healthy behavior (e.g., exercise), or assisting in the management of disease (e.g., medication management) (Ford et al., 2009). However, if this support is in the form of overprotection, for example, it may cause more harm than good (Bertoni et al., 2023). Satisfying relationships are associated with lower rates of mental health problems and better quality of life in cardiac patients, whereas discord can exacerbate anxiety and depression (Bouchard et al., 2021; Bouchard et al., 2023), increasing the risk of cardiac complications and death (Civieri et al., 2024).

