## Study aims and objectives

The primary aim of this RCT is to examine the efficacy of the 8-week HHT program on the relationship quality of patients with CVD and their romantic partners at 8 weeks, in comparison to UC. We expect that those assigned to the HHT condition will have greater improvements in RQ scores (as measured by the dyadic adjustment scale) than will those in UC. Secondary aims include measuring the impact of the program on relationship quality at 6 months and secondary outcomes, including cardiovascular and cortisol reactivity, inflammatory markers, mental health, quality of life, health behaviors, and cardiovascular risk factors, at 8 weeks and 6 months. We expect greater improvements in all secondary outcomes among HHT participants than in UC participants. This paper describes the study design, objectives and method.

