## Method

### Design

The study is a single-centre, RCT with parallel group design. After a baseline assessment, participants are randomized in a 1:1 fashion, using a computer-generated sequence utilizing permuted blocks of 4, 8 and 10 initiated by the institutional methods centre, to the HHT program or to UC. Since sex and participation in CR can have an impact on the study outcomes, randomization is stratified by patient sex (male/female) and participation in the University of Ottawa Heart Institute (UOHI) CR program (yes/no). The trial began in October 2019 and data collection is ongoing. The protocol was approved by our institutional research ethics board (OHSN-REB# 20190101-01H) and all participants provide informed consent. Figure 1 depicts the study design and cohort flow.

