#### Health behaviors

Smoking status is reported by participants and confirmed with CO concentration (<10 ppm) in an expired breath sample, using the Russell standard (West et al., 2005). Participants wear an *ActiGraph GT3X-BT accelerometer* on their non-dominant hand for 7 days to assess physical activity and sedentary behaviors. Self-reported frequency and duration of mild, moderate and vigorous physical activity is also measured using a modified and validated version of the *Godin Leisure Time Exercise Questionnaire (GLTEQ)* (Godin and Shephard, 1985). Two *adherence* measures are used: (1) Medication adherence is measured with 3-items (e.g., how often do you forget to take your medication?) and (2) CR adherence is calculated by the percentage of exercise sessions attended relative to those prescribed.

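### CR adherence exists only for patients who enrol in CR, which can happen after randomisation, so an arm comparison of this percentage would not be intention-to-treat

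*Protocol article*

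**What the plan says.** All places are in the protocol article.

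- **Who has data.** Measures: "CR adherence (if enrolled) is collected for patients only". Table 1 schedules CR adherence for patients at baseline, week 8 and week 24.
- **Definition.** Health behaviors: "CR adherence is calculated by the percentage of exercise sessions attended relative to those prescribed".
- **Uptake is voluntary.** Usual care describes automatic referral to CR, but "patients may choose whether they wish to receive these services or not".
- **Uptake is recorded after allocation.** Follow-up assessments: "Patients also report if they enrolled in CR and, if so, in which program options they participated".
- **Role of the outcome.** Study aims and objectives lists the secondary outcomes as including "mental health, quality of life, health behaviors, and cardiovascular risk factors, at 8 weeks and 6 months", and adds: "We expect greater improvements in all secondary outcomes among HHT participants than in UC participants". CR adherence is one of the measures described under Health behaviors.
- **Stratification.** Design: randomisation is stratified by patient sex and by "participation in the University of Ottawa Heart Institute (UOHI) CR program (yes/no").
- **Analysis set.** Planned statistical analyses gives intention-to-treat as the general rule. It puts secondary outcomes in a repeated-measures multilevel model fitted by full maximum likelihood. It gives no separate rule for patients who have no CR adherence value.

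**The concern.** The percentage has a denominator only when sessions have been prescribed. Whoever follows the plan as written can compare it only between HHT enrollees and usual care (UC) enrollees. Some of those patients may enrol after allocation, so randomisation does not guarantee that the two enrolled groups are alike.

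If HHT brings in patients who would otherwise have stayed out of CR, the HHT enrollees include a type of patient who is absent from the UC enrollees. A difference in mean adherence then mixes any effect on adherence with a change in who is measured. The result could point the opposite way from the effect on CR actually received. A reader told that all analyses are intention-to-treat would have no warning of this.

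**Working it through.** **1. What follows from the text alone.** Adherence = sessions attended / sessions prescribed. With nothing prescribed this is 0/0, which is undefined rather than missing. A maximum-likelihood model fitted to the percentage either leaves never-enrolled patients out or treats them as having an unobserved value. Neither describes a patient whose attendance was in fact zero. Because uptake is a choice and is asked about at both follow-ups, the subset with a value can change after allocation. Stratification balances CR status at allocation but not later enrolment.

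**2. Is there a plan figure to reproduce?** No. The documents give no CR uptake by arm, no mean or SD of adherence, and no relation between uptake and adherence. Every figure below is assumed and only illustrative.

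**3. Simple mixture.** Assume 50% of UC patients enrol and average 70% adherence. Under HHT the same 50% enrol and adhere equally, and a further 10% enrol with adherence *a*.

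HHT mean among enrollees = (0.50 × 70 + 0.10 × *a*) / 0.60

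HHT mean among all randomised, never-enrolled = 0: 0.50 × 70 + 0.10 × *a*

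| *a* | HHT enrollees | UC enrollees | HHT, all | UC, all |
|---|---|---|---|---|
| 40% | 39/0.60 = 65% | 70% | 39% | 35% |
| 70% | 42/0.60 = 70% | 70% | 42% | 35% |
| 90% | 44/0.60 = 73.3% | 70% | 44% | 35% |

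The enrollee comparison is 5 points against HHT, null, or 3.3 points in its favour, depending only on who the added enrollees are. No patient who would have enrolled anyway adheres differently in any row.

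**4. Normal selection model.** A patient enrols when a latent propensity passes an arm-specific threshold. Propensity and adherence have correlation *r*, the adherence SD is 25 points, and HHT has no effect on adherence itself. With uptake *p* and *z* the corresponding normal threshold:

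Spurious HHT − UC difference among enrollees = 25 × *r* × [φ(z_HHT)/p_HHT − φ(z_UC)/p_UC]

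φ(z)/p is 0.798 at 50%, 0.644 at 60% and 0.497 at 70% uptake. For 50% vs 60% and *r* = 0.5: 25 × 0.5 × (0.644 − 0.798) = −1.9 points.

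| Uptake UC vs HHT | *r* = 0 | *r* = 0.3 | *r* = 0.5 | *r* = 0.8 |
|---|---|---|---|---|
| 50% vs 50% | 0 | 0 | 0 | 0 |
| 50% vs 60% | 0 | −1.2 | −1.9 | −3.1 |
| 50% vs 70% | 0 | −2.3 | −3.8 | −6.0 |

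The largest value is 6.0/25 = 0.24 SD. The minus sign comes from assuming *r* > 0; a negative *r* reverses it.

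**5. Allowing for patients already in CR.** Suppose the 20% to 60% of patients with the highest propensity are in CR at randomisation, and HHT raises uptake among the rest by 20 points (from 20% to 40%, or from 30% to 50%). With *r* = 0.5 the difference lies between −3.4 and −1.5 points. It is smaller the more patients are already in CR, but it is not zero.

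**6. All randomised patients.** With latent mean adherence 70, *r* = 0.5 and uptake 50% vs 70%, enrollees average 80.0 (UC) and 76.2 (HHT). With never-enrolled as zero, the means are 0.50 × 80.0 = 40.0 and 0.70 × 76.2 = 53.3. The sign reverses between the two measures.

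**The case against.** The article never states an enrollee-only comparison. It says the measure is collected if the patient is enrolled, and how to treat undefined values is usually settled in an analysis plan, which is not shown. This stands as a limit on the wording: a reader might infer that the plan explicitly specifies the flawed comparison, and it does not. But the restriction comes from the outcome's stated definition, and the article does call for between-arm comparison of health behaviors, so it is more than an omitted detail.

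A reader might also infer that the trial's own rationale expects HHT to change who enrols. The text does not go that far. The Background says "better marital adjustment and positive dyadic coping is associated with enhanced medication compliance" and, in the same sentence, extends the association to CR. That is an association, and it does not mention enrolment. It makes an effect on uptake plausible but does not predict one.

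Many enrolment decisions may precede allocation: referral is automatic, patients may join up to 6 months after the event, and CR participation is known at randomisation. That would shrink the problem, as step 5 shows, but enrolment is still asked about at follow-up. The planned stratified analyses by CR participation would supply part of the remedy if they use status at randomisation; the article does not say at what time participation is judged.

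Finally, counting never-enrolled patients as zero measures CR exposure, not adherence given prescription. That is correct, which is why it is proposed only as a supporting measure.

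**Conclusion.** The point holds in a limited form. As defined, CR adherence has a value only in a subset that can form partly after randomisation, so a between-arm comparison of the percentage would not be intention-to-treat as the analysis section states.

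Bias needs two conditions: HHT must alter uptake, and the added enrollees must adhere differently from those who would enrol anyway. If either fails, there is none in these illustrations. A reader might infer that HHT is bound to look worse. The documents do not support that; the direction depends on who the added enrollees are. The illustrative 1 to 6 points rest wholly on assumed uptake, SD and correlation, so the true size is unknown.

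This concerns one secondary measure. The primary DAS comparison is untouched, and the point is minor.

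**What to change.** 1. Compare CR enrolment by follow-up between arms, as a binary outcome in all randomised patients.
2. Add sessions attended in all randomised patients, with never-enrolled counted as zero, as a supporting measure of CR exposure.
3. Confine the randomised comparison of percentage adherence to patients with CR participation = yes at randomisation, a stratum fixed before allocation.
4. Label percentage adherence among all enrollees as descriptive.
5. State that the planned stratified analyses by CR participation use status at randomisation.

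**Cost.** Analysis-plan wording and one recoded variable. Enrolment is already asked at follow-up, attendance is already needed for the percentage, and the stratum is known. The article reports data collection as ongoing, so this can still be prespecified. The all-patient measure will contain many zeros and needs a model that allows for them, and it answers a different question from adherence given prescription. Restricting the percentage to the pre-randomisation stratum also leaves fewer patients in that comparison.
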